#### PAT implementation plan

Each site will complete an implementation plan, describing who will be screened, where results will be stored, how results will be communicated to families and to staff, and how results will be used (develop a formal implementation blueprint). For TIER, the plan includes the responsibilities of the champion.

#### Strategy I

For sites randomized to strategy I, the webinar is the implementation condition. Sites will receive technology support, as needed, throughout the implementation period. These strategies correspond to implementation strategies—creating a structure for implementation including creating implementation teams and developing an implementation plan [37].

#### Strategy II

Strategy II includes the webinar and technical support as above with the addition of two evidence-based resources that may improve implementation. The site PI and center staff conducting screening will participate in a monthly 1-h consultation call (provide ongoing consultation, create a learning collaborative) with other TIER sites in that cohort. The group format of this strategy is intended to foster group problem-solving and peer support about issues in implementation. Sites will identify a champion (identify and prepare champions) who will advocate for PAT implementation and support staff in screening activities by serving as a resource to problem-solve and communicate with the broader clinical staff about screening and psychosocial risk. The champion will likely be a clinical leader with enthusiasm and commitment to universal psychosocial risk screening.

#### Measurement/outcomes (all sites)

The measures assess outcomes across patient/family, provider, and institution levels (Table 1) that are clearly operationalized and reproducible [46]. Site PIs and coordinators will attend training on data collection procedures, in separate sessions for the two conditions.

**Table 1 Tab1:** Measurement

Level/Hyp	Concept	Source	Metric/measure
Patient/family 2.1	Penetration Health equity	EHR (monthly)	Demographics: race, ethnicity, zip code, insurance No. eligible families, English/Spanish No. eligible families screened, English/Spanish % Family feedback letter provided
Provider 2.2	Feasibility Appropriateness Acceptability Engagement in addressing health disparities Job satisfaction Burnout	Survey (Pre, 6-month, Post)	Acceptability of intervention measure Intervention appropriateness measure Feasibility of intervention measure AREA scale of physician engagement Satisfaction employees healthcare Maslach Burnout Inventory version for Medical Personnel
Institution 2.3	Adoption Sustainability: perceived benefit Cost-effectiveness: services/need and cost	Survey	Site participation rate PAT implementation questionnaire
		EHR (monthly)	Psychosocial Services and Medical Treatment Checklist Intensity of Treatment Rating Scale

At the patient/family level (Hyp 2.1) the site coordinator will extract EHR data and send the coded data via REDCap to the data core. The following data for English and Spanish versions of the PAT will be reported monthly: new patients meeting eligibility requirements per the PAT implementation plan; patients with documentation of PAT screening; patients receiving feedback letter; demographic data on all eligible and all screened (race, ethnicity, zip code, insurance).

At the provider level (Hyp 2.2), the site PI and screeners will complete the following self-report measures (~ 15 min) at baseline (T1), and 6 (T2) and 12 (T3) months via REDCap: acceptability of intervention measure; intervention appropriateness measure and feasibility of intervention measure [47]; measure of physician engagement in addressing racial and ethnic health care disparities [48], satisfaction of employees in healthcare survey [49], and Maslach Burnout Inventory [50].

The outcomes at the institution level (Hyp 2.3) are as follows: adoption, the intention of sites to use the PAT (the ratio of sites that initiate the study); whether screening is perceived as an asset to the institution using the PAT Implementation Questionnaire (PIQ) [35] which will be completed by the site PI, the screeners, and the champion at T1, T2, and T3; whether services are matched to the needs of families based on PPPHM levels using EHR data using the Psychosocial Services and Medical Treatment Checklist (PSMTC) [18] at 30, 60, and 90 days; cost using the data from the PSMTC to estimate the amount of psychosocial staff time and national median hourly salary data [51–53]. The Intensity of Treatment Rating Scale (ITR-3) [54] will be completed at the 90-day post-screening data collection time point based on diagnosis, stage, and treatment.

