**Fig. 1 Fig1:**
[figure not shown]
Pediatric Psychosocial Preventative Health Model

Empirical evidence supports the readiness of the PAT for broad implementation. It is used in 28.9% of pediatric cancer programs in the USA [11] and widely in other countries [20–28]. The PAT is acceptable to families across race, ethnicity, and SES [7, 8, 10, 16, 17, 29] and has been shown to impact psychosocial outcomes at higher levels of distress when results are shared with staff [30]. We adapted the PAT for hematopoietic stem cell transplantation (HCST) [31] including development of a clinical pathway to facilitate its integration in clinical care [32, 33], and in sickle cell disease, adding items to capture relevant aspects of the social context for families (e.g., school absences, changes in housing) [34].

We do not know the extent to which the PAT has been adopted, whether implementation is consistent across families, and if PAT implementation is sustained. The best practices for implementation have not been studied, and barriers and facilitators to systematic implementation have not been evaluated. Challenges such as time, determining who will screen, technical difficulties, and linking screening to care were potential barriers. In a pilot of an implementation model using a workshop and consultation calls in three states, 9 of 12 centers successfully implemented the web-based PAT, half using both the English and Spanish versions [35]. The pilot data informs the implementation and measurement strategies in this study.

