**Fig. 2 Fig2:**
[figure not shown]
Interactive systems framework and stages of the implementation study

#### Aim 1

Refine strategies I (training) and II (TIER) using semi-structured interviews with stakeholders—parent advocates, multidisciplinary health care providers, national pediatric oncology professional organizations, and health care industry leaders (implementation team).

#### Aim 2

Compare the two theoretically based and empirically informed strategies to implement the PAT in English and Spanish using a cluster-randomized controlled trial. Compared to training:

**H2.1**. At the patient/family level, TIER will be associated with: (a) a higher proportion of families of newly diagnosed children screened and provided with feedback (penetration) and (b) higher rates of screening for ethnic minority and socioeconomically diverse families (health equity).

**H2.2**. At the provider level, TIER will be (a) more feasible and rated as appropriate and acceptable, (b) associated with greater engagement in addressing health disparities, and (c) associated with less burnout and better job satisfaction.

**H2.3**. At the institution level, TIER will be associated with: (a) a higher rate of site participation (adoption), (b) more positive perceptions of implementation benefits and fewer challenges (sustainability), and (c) psychosocial care better matched to need demonstrating a more equitable distribution of services and costs of care.

#### Aim 3

Based on the results of the trial and further guidance from the implementation team, we will integrate acceptable, feasible, and effective strategies to develop and disseminate a web-based PAT Implementation Toolkit.

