## Methods and design

### Overview of the study

The aim of this mixed methods research is to implement universal, systematic family psychosocial risk screening with the PAT in English and Spanish to assure that *all* families of children newly diagnosed with cancer at the participating cancer centers are screened. The setting/context of the research is pediatric cancer programs in the USA. The approach, reflected in the three aims, is guided by the ISF [36]. We selected specific implementation strategies from the Expert Recommendations for Implementing Change (ERIC) project [37] targeting implementation outcomes at three levels (patient/family, provider, institution). ERIC strategies utilized are noted in parentheses throughout this article.

Aim 1 corresponds to the first component of the ISF, Prevention Synthesis and Translation System. We will prepare programs to implement the PAT by conducting qualitative semi-structured interviews with a diverse set of stakeholders (*n* = 19). Interviews will be focused on details of strategy I (training via webinar) and strategy II (training + TIER—consultation calls and identification of a champion), followed by questions about facilitators and barriers, and about implementation strategies and resources needed for universal screening and care delivery to address health inequities. We anticipate fine-tuning and adding components to improve penetration and health equity targets, acceptability and feasibility, adoption, and sustainability.

The activities of aim 2 correspond to the second component of the ISF, Prevention Support System. Support for those implementing innovation occurs at multiple levels within the system—*patients/families, providers,* and *institution.* To implement the PAT in English and Spanish, 18 pediatric cancer programs, of varying sizes and with geographic distribution assuring representation of ethnic and racial minority families and families at socioeconomic risk, have agreed to participate. We will conduct a cluster-randomized comparative effectiveness trial of the two implementation strategies across three cohorts stratified by size of site based on new patients per year (Fig. 3).

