H2.1. ANOVA will compare the effectiveness of the two implementation strategies on penetration and health equity. The outcomes are proportions: families screened/families eligible, families provided feedback/families screened, ethnic minority families screened/ethnic minority families eligible, low SES families screened/low SES families eligible. ICCs among the clusters will be calculated and used to adjust for the cluster effect [67, 68].H2.2. Three sets of outcome variables—perception of implementation, engagement in addressing health disparities, and burnout/job satisfaction—will be tested. A two group analysis using Structural Equation Modeling (SEM) will compare the effectiveness of the two strategies [69, 70]. To test the effect of time, we will conduct latent growth curve analysis [71–73]. Analyses will be conducted using Mplus 5.0 [74] with ML estimation for outcome variables that meet the distribution assumptions, and WLSMV estimation for variables that do not. Potential mediating effects of favorable perception of implementation on provider job satisfaction and burnout will be examined using mediation models. TIER is expected to be associated with more favorable perceptions of implementation, less burnout, and higher job satisfaction.H2.3. At the institution level, adoption of the PAT will be measured by a ratio of sites that initiate implementation/sites that agreed (H2.3a). If substitutions are necessary, sites that are newly invited will be added to the denominator and adoption calculated by total acceptances/total invited. ANOVA will be conducted to compare the effectiveness of the two strategies. For H2.3b sustainability (PIQ perceptions of implementation benefits and challenges), ANOVA will be conducted to compare the effectiveness of the two strategies on benefits and challenges. For H2.3c, we are interested in the extent to which psychosocial care is matched to need. A cost-effectiveness threshold or criterion to which to compare costs of screening with these two implementation strategies has not been established, necessitating our consideration of valued outcomes in the psychosocial screening literature and resources available. We will use a data analytic approach that we used previously [18]. ANOVA will be conducted to test whether psychosocial care is matched with levels of psychosocial risks, resulting in a 2 (strategy) × 3 (psychosocial risks: clinical, targeted, universal) design on equitable distribution of services and costs of care. It is expected that the 3 PPPHM levels will be related to number and costs of services provided as measured on the PSMTC, with least at universal and most at clinical. It is expected that TIER will result in a better match between level of risk and services provided. Scores from the PSMTC will be derived and mapped onto the levels of the PPPHM. Additional analyses will be conducted to compare English speaking and Spanish speaking families, different ethnicity, race, and SES and insurance status on the outcome variables for H2.3c.

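### The screening proportions in H2.1 are divided by a count that each site's own implementation plan defines, not by all newly diagnosed families

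*Protocol article*

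**What the plan says.** - **Measurement/outcomes (all sites), Hyp 2.1.** Site coordinators report each month, for the English and Spanish versions, the number of "new patients meeting eligibility requirements per the PAT implementation plan", together with patients screened and patients given a feedback letter. Demographics are listed for eligible and screened patients. Neither this section nor Table 1 lists a count of every new patient regardless of the plan.
- **PAT implementation plan.** "Each site will complete an implementation plan, describing who will be screened". The same section adds: "For TIER, the plan includes the responsibilities of the champion".
- **Data analysis, Aim 2, H2.1.** Penetration is "families screened/families eligible". Health equity is "ethnic minority families screened/ethnic minority families eligible", with a matching ratio for low-SES families. The fourth proportion, feedback among those screened, does not use the eligible count.
- **Specific aims, H2.1a.** TIER is expected to give "a higher proportion of families of newly diagnosed children screened and provided with feedback (penetration".
- **Overview of the study.** The aim is that all "families of children newly diagnosed with cancer at the participating cancer centers are screened".

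**The concern.** The hypothesis and the aim concern one population, and the measured outcome uses another. The sample size of 2946 is also built from new patients per year, not from plan-eligible ones.

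The plan is part of the implementation under test, so the denominator may respond to the strategy being compared. A ratio whose denominator can move with the intervention no longer compares like with like. An arm can look better because its plans leave out families who are hard to screen. It can look worse because its plans take them in. The equity outcomes are the most exposed, since the families easiest to leave out are those H2.1b is about.

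The listed data could not repair this later, because a family outside the plan would not appear in them.

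**Working it through.** The protocol gives no figure for this point, so there is none to reproduce. The check asks how far the ratio can move.

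**Inputs.** From the protocol: 9 sites and a stated effective sample of 950 per arm, one-sided alpha 0.05, 80% power. Assumed, because the protocol gives no values: p = 60% of all new families screened when the plan omits nobody; e = share of new families a plan omits (5%, 10%, 20%); q = rate at which the omitted families would have been screened.

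**Formulas.** Reported penetration = (p − e·q)/(1 − e). Share of all new families actually reached = p − e·q.

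| q | e = 5% | e = 10% | e = 20% |
|---|---|---|---|
| 0%: reported | 0.60/0.95 = 63.2% | 0.60/0.90 = 66.7% | 0.60/0.80 = 75.0% |
| 0%: reached | 60% | 60% | 60% |
| 30%: reported | 0.585/0.95 = 61.6% | 0.57/0.90 = 63.3% | 0.54/0.80 = 67.5% |
| 30%: reached | 58.5% | 57% | 54% |
| 60%: reported | 60% | 60% | 60% |
| 60%: reached | 57% | 54% | 48% |

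With q = 0 the reported rate rises and no extra family is screened. With q = 30% it rises while fewer families are reached. With q = 60% the ratio does not move. With a denominator of all new patients, the q = 0 case gives 60% in both arms and a difference of zero.

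**The opposite direction.** Suppose Strategy I plans omit 20% who are never screened, and report 60/80 = 75%. Suppose TIER plans omit nobody, screen the same 75% of the other 80%, and screen 30% of the remaining 20%. TIER reaches 0.75 × 0.80 + 0.30 × 0.20 = 66% and reports 66%. It reaches 6 points more families and reports 9 points less.

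**Scale.** At 950 per arm the detectable effect is h = (1.645 + 0.842) × √(2/950) = 0.114, or about 5.5 points above 60%. If every site in one arm narrows, none in the other does, and q = 0, the chance of declaring a false difference is about 41% (e = 5%), 92% (10%) and over 99% (20%). For the one-sided test that arm would have to be TIER.

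**If only some sites narrow.** With nine equally weighted sites, each narrowing site moves its arm by one ninth of its own shift:
- e = 5%: 3.2/9 = 0.36 points per site. All nine together give 3.2 points, short of 5.5.
- e = 10%: 6.7/9 = 0.74 points per site. 5.5/0.74 = 7.4, so eight sites are needed.
- e = 20%: 15/9 = 1.67 points per site. 5.5/1.67 = 3.3, so four sites are needed.

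**The case against.** A reader might infer more than the documents support.

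- **An English-only plan.** It is tempting to say that a site could list English only and turn 60% into 60/86 = 70%, using the protocol's 412/2946 = 14%. The 18 programs agreed to implement both languages, the monthly data cover both versions, and Table 1 requires the eligible count by language. Such a plan would depart from the protocol. The 412 are Hispanic caregivers able to complete the Spanish version, and nothing says they cannot complete the English one, so 14% is only an upper bound. The pilot remark, "half using both the English and Spanish versions", does not say that the other centers excluded anyone by plan. A one-site shift of 9.8 points also moves a nine-site arm by only 9.8/9 = 1.1 points, so it cannot be set against a between-arm difference of 5.5.
- **Plans known to follow randomisation, or expected to be narrowed.** The article gives no date for the plan. The timing is inferred from the champion sentence; that is a reasonable inference but not a stated fact. Nothing says sites will narrow their plans, that narrowing would differ by arm, or that plans are revised during the year. The stated intent is universal screening.
- **A condensed article.** The full protocol may contain a plan template or common criteria that limit what sites can vary. If so, the concern shrinks. Still, the article does state the denominator and ties it to the site plan, so this is not a detail left unsaid.
- **The remedy.** A bare count of all new patients has no place for caregivers who read neither English nor Spanish. That is correct, and some central exclusion rule is needed.

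These points limit the size that can be claimed. They do not remove the mismatch between the population of the hypothesis and the denominator of the outcome.

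**Conclusion.** The point holds as a defect in the outcome definition. Three of the four H2.1 proportions use a denominator set site by site, probably with the strategy known. It differs from the population in H2.1 and the aim, and the listed data would not allow it to be reconstructed.

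The size of any bias is unknown. A false difference needs both of two things: plans that differ between arms in whom they omit, and omitted families who would be screened less often than the rest. Equal narrowing in both arms with equal true rates gives no false difference, and omitting families who would be screened at the same rate leaves the ratio where it was. The 63.2%, 66.7% and 75.0% are the extreme case of a whole arm narrowing with omitted families never screened. They show what the definition permits and are not a forecast. Bias in either direction is possible.

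**What to change.** Define one denominator in the protocol for overall, ethnic-minority and low-SES screening, identical at every site and in both strategies: all patients newly diagnosed at the site in its cohort year. Fix any exclusion centrally before randomisation, for example caregivers who read neither English nor Spanish.

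Add to the monthly extraction a count of all new patients, with the same demographic items and language, whether or not the site plan covers them. Keep eligibility under the site plan as a descriptive or fidelity measure, reported by strategy so that any difference in plan scope can be seen.

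The cost is a change of wording and slightly more extraction by the same coordinators from the same EHR. Reported penetration may look lower than under the plan-based ratio.

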#### Participants

Since screening will be integrated into the clinical services of the centers, it will be routine clinical care. Coded EHR data with minimal protected health information (PHI) will be collected for patients. Reflecting the importance of staff in implementation [45], consented participants include the site PI and screeners and, in strategy II, the champion.

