PAT implementation will be tested using a head-to-head randomized implementation (comparative effectiveness of two implementation strategies) trial in three cohorts over 3 years. *Randomization*. Eighteen sites will be randomized to one of three cohorts. Each cohort will be further randomized to one of the two strategy conditions. Randomization will stratify sites by size to maximize internal validity and statistical power. Sites will be randomized by a data analyst not connected with the study using a two-step Excel = RAND() function. The sequence will be stored in a password-protected electronic file. *Sample size*. The estimated sample of patients/families is based on the median number of new patients each year from the PIPS-CSS database: small (*n* = 60), medium (*n* = 92), large (*n* = 339) multiplied by 6 sites at each size, a total of 2946, with 1473 families allocated to each strategy. With an anticipated Interclass Correlation Coefficient (ICC) [65] of .005, the effective sample size is 950 per arm, a sample size that is sufficient to detect a small effect between the two strategies given 80% power (alpha = .05, one sided). We project a Hispanic sample of 20% of the total (*n* = 589). Based on our research [8], approximately 30% of Hispanic caregivers will be more acculturated/not literate in Spanish at the level necessary to complete the Spanish PAT, rendering a sample of 412. With an anticipated ICC of .005, the effective sample size is 224 which is sufficient to detect a medium effective between the English and Spanish versions given 80% power (alpha = .05, one sided). At the provider level, each of 18 sites has a PI and up to four people screening, and for TIER sites, a champion. Therefore the staff sample ranges from a minimum of 45 ([18 × 2] + 9) to a maximum of 99 ([18 × 5] + 9), likely in the middle given the range of size of sites. At the institution level, 18 sites will be randomly assigned to one of two strategies (9 sites/group). These sample sizes are comparable to other implementation science studies [66].

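### The PIQ comparison for H2.3b pools champions with other raters in TIER only, so a difference favouring TIER could reflect who was asked

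*Protocol article*

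**What the plan says.** **Who rates.** In the protocol article, Measurement/outcomes (all sites), the PIQ is the instrument "which will be completed by the site PI, the screeners, and the champion at T1, T2, and T3". The same section limits the provider measures for H2.2 to two roles: "the site PI and screeners will complete the following self-report measures".

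**Who exists in each arm.** The Participants paragraph for the aim 2 trial says that "consented participants include the site PI and screeners and, in strategy II, the champion". Under Strategy I, "For sites randomized to strategy I, the webinar is the implementation condition", with technology support as needed and no champion. Under Strategy II, "Sites will identify a champion (identify and prepare champions) who will advocate for PAT implementation", and "The champion will likely be a clinical leader with enthusiasm and commitment to universal psychosocial risk screening".

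**What is compared.** H2.3b predicts more positive perceptions of benefits and fewer challenges under TIER. The H2.3 analysis paragraph (aim 2, below Data cleaning and missing data) says: "ANOVA will be conducted to compare the effectiveness of the two strategies on benefits and challenges". It mentions no restriction by role, no term for role and no use of T1. Data cleaning and missing data names only program size and cohort as factors to be controlled if needed.

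**Sample.** The aim 2 sample-size text, speaking of the provider level, says: "Therefore the staff sample ranges from a minimum of 45". The maximum it gives is 99, and both figures count nine champions as people additional to the PIs and screeners.

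**The concern.** Read together, these sections have the training arm rated by two roles and TIER by three. The third role is itself a component of the strategy under test, and its holder is asked to promote screening. The PIQ then asks whether screening is an asset to the institution. An all-rater comparison therefore mixes two things: any effect of TIER on the PIs and screeners found in both arms, and the presence of an extra group of raters in one arm.

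At stake is the interpretation of H2.3b. TIER could look more sustainable with no change in any PI's or screener's view. Aim 3 draws on the trial results to decide what goes into the toolkit, so the reading of this outcome has a use beyond the trial report.

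A smaller question is whether the staff sample of 45 to 99 fits the H2.2 measures, which champions are not asked to complete.

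**Working it through.** **Inputs from the protocol article.** There are 18 sites, 9 per strategy. Each has one PI and up to four screeners, and the stated minimum implies one screener. Each TIER site adds one champion. Write s for screeners per site.

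**Reproducing the stated sample.** Total = 18 × (1 + s) + 9.
- s = 1: 18 × 2 + 9 = 45.
- s = 4: 18 × 5 + 9 = 99.

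Both stated figures reproduce exactly.

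**Split by arm.** TIER = 9 × (1 + s) + 9; training = 9 × (1 + s).
- s = 1: 27 v 18.
- s = 4: 54 v 45.

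**Champion share of TIER raters.**
- s = 1: 9/27 = 33.3%.
- s = 4: 9/54 = 16.7%.
- Training arm: 0% in both cases.

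Averaging to site level does not remove this. At a TIER site the champion is one of three to one of six raters, so the site mean carries the same share.

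**Shift with no true effect.** Shift = share × d, where d is how many SDs more favourably champions rate than PIs and screeners. The article gives no value for d, so the values below are assumptions.

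| Assumed d (SD) | Shift, minimum staffing (SD) | Shift, maximum staffing (SD) |
|---|---|---|
| 0.2 | 0.07 | 0.03 |
| 0.5 | 0.17 | 0.08 |
| 0.8 | 0.27 | 0.13 |

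**Illustrative error rate.** Take a one-sided 5% test, SD 1, independent raters and SE = √(1/n_TIER + 1/n_training). The SE is √(1/27 + 1/18) = 0.304 at minimum staffing and √(1/54 + 1/45) = 0.202 at maximum. The chance of a false result favouring TIER is 1 − Φ(1.645 − shift/SE). For d = 0.2, 0.5 and 0.8 this gives:
- minimum staffing: 7.7%, 13.6% and 22.1%;
- maximum staffing: 6.9%, 10.9% and 16.2%.

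The article states the one-sided 5% level for its family-level calculations, not for H2.3b. The calculation also ignores clustering by site. These rates are indicative only.

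**Restricted to common roles.** There are 9 × 2 = 18 raters per arm at minimum staffing and 9 × 5 = 45 at maximum. The champion share is zero, so the shift from rater mix is zero whatever d is. On the same assumptions the SE becomes √(2/18) = 0.333 and √(2/45) = 0.211, which is about 10% and 4% larger than with champions included.

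**H2.2 sample.** PIs and screeners alone number 18 × 2 = 36 to 18 × 5 = 90.

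**The case against.** **Inclusion in the test is inferred.** The measurement section describes data collection, and the analysis sentence does not say whose ratings enter. A fuller analysis plan could restrict the raters or use T1. That is fair, and it limits the claim: the article sets up unequal rater pools and does not exclude the extra role from the comparison. It is still more than an omitted detail, because the article fixes both the raters and the comparison, and for H2.2 it already uses only roles present in both arms.

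**Bias toward TIER is not established.** A reader might infer that champions are chosen for enthusiasm and that H2.3b is therefore biased by a known amount. The documents do not support that. The champion will only likely be enthusiastic, and no PIQ scores by role are given. PIs in both arms come from programs that all agreed to take part, so they may be favourable too. A champion whose task includes problem-solving might report more challenges, which would work against TIER. The stated advocacy role makes a favourable tilt plausible; its size, and its direction on challenges, remain open.

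**T1 ratings could absorb stable enthusiasm.** They could if change from T1 were analysed, but the article does not commit to that for H2.3b.

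**Champions might double as PI or screener.** That would shrink the problem, but the sample-size text counts them as additional people.

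**The reach is limited.** This stands. H2.3b is one of several sub-hypotheses. The EHR-based outcomes and the H2.2 measures are not affected by this difference in raters.

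**Conclusion.** The point holds as a design weakness in one secondary comparison. The rater pools for the PIQ differ by strategy by design, randomisation cannot correct this, and the stated ANOVA does not remove it. A difference favouring TIER on H2.3b could reflect who was asked.

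The firm figures are the shares: champions are 33% to 17% of TIER raters and none of the training raters. These rest on the article's staffing range and on champions being separate people. The shifts of 0.07 to 0.27 SD (minimum staffing) and 0.03 to 0.13 SD (maximum) depend wholly on the assumed rating gap of 0.2 to 0.8 SD and should be read as illustration.

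A reader might also infer that the staff sample of 45 to 99 is an error. It is not: it is correct for consented staff and for PIQ raters as planned. The mismatch is only with H2.2, where the measures go to 36 to 90 people. No power or detectable effect is computed from that range, so no stated result changes.

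**What to change.** State that the between-strategy PIQ comparison for H2.3b uses ratings from site PIs and screeners only, as the article already does for the H2.2 measures. Report champions' PIQ ratings descriptively within TIER. Settle this before the PIQ data are compared by strategy.

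In the sample-size text, keep 45 to 99 for consented staff and planned PIQ raters. State 36 to 90 for the H2.2 measures and 18 v 18 to 45 v 45 for the restricted PIQ comparison.

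The cost is a change of wording and up to 9 fewer TIER raters in the comparison. Data collection does not change, and champions' ratings are still reported.
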